## Abstract

**Background::**

Patients, particularly those at the end of their lives, frequently receive goal-discordant care, and their surrogate decision-makers suffer long-term psychological injury. Contributors to these issues may include infrequent communication between clinicians and surrogates, failure to discuss prognosis, values, and treatment options that include comfort-focused care, and surrogates facing high-stakes decision-making while underprepared and overwhelmed psychologically and emotionally.

**Design::**

This is a multicenter, patient-randomized efficacy trial of a multi-component intervention, versus usual care, for 370 incapacitated, critically ill adults at high risk of death or severe disability, and their surrogate decision-makers, from 7 hospitals across the United States.

**Intervention::**

The intervention combines surrogate utilization of a digital Family Support Tool (FST) in real-time during their loved one’s hospitalization with proactively scheduled family meetings, for which both surrogates and clinicians receive additional preparation, at set intervals during the ICU hospitalization. Those in the control arm will receive usual ICU care.

**Outcomes::**

Our primary outcome is patient-centeredness of care, measured using the modified Patient Perceived Patient-Centeredness of Care (PPPC) scale. Secondary outcomes include surrogates’ psychological symptom burden, communication and decision quality, and patients’ health resource utilization and clinical outcomes.

**Conclusion:**

This trial will provide robust evidence about the impact of combining the FST with increased and intentional communication, on patient, family, and health system outcomes for those hospitalized in the ICU.

## Background

1.

Up to a quarter of the time, patients receiving care toward the end of their life receive treatment that is inconsistent with their values and preferences, typically comprising more invasive and burdensome therapies than they would choose for themselves [1–3]. At the same time, medical care at the end of a patient’s life is a key contributor to health care costs, accounting for 25% of Medicare costs [4]. Regardless of whether patients are facing the end of their life or other challenges related to critical illness, family members faced with serving as surrogate decision-makers for their loved ones suffer psychological distress (including lasting psychological harms such as depression, anxiety, and post-traumatic stress disorder), guilt, and doubt about their decisions [5–9]. Multiple factors contribute to these growing problems, including (1) infrequent communication between clinicians and surrogates, (2) frequent failure to discuss prognosis, values, and treatment options that include comfort-focused care, and (3) surrogates facing high-stakes decision-making while underprepared and overwhelmed psychologically and emotionally.

We sought to design a scalable, in-the-moment, feasible intervention that combined an interactive digital tool with systems-level care delivery changes in order to attend to these three mechanisms contributing to goal-discordant care and surrogate psychological harm in critical illness. Our goals were to design an intervention that is easy to use, scalable to diverse health systems, and applicable to a broad range of diseases that cause critical illness [10–14]. Existing evidence shows that family support interventions delivered by trained interventionists can improve outcomes [15,16]. However, such interventions require adding people to the ICU team, making these interventions expensive and difficult to scale due to the amount of training required [9,17,18]. We therefore developed a multi-component intervention that involves increased targeted communication between existing clinicians and families via proactive family meetings scheduled at set intervals, unlimited access to an interactive digital tool (the Family Support Tool, or FST) for family emotional support and decisional preparation, and feedback to clinicians in advance of family meetings regarding family questions, expectations about prognosis and treatment leaning. We previously conducted pilot testing of the web-based FST, followed by a two-arm, patient-level randomized pilot trial comparing the FST to enhanced usual care, establishing feasibility of recruitment and retention (with 96% of enrolled participants using the tool per protocol), as well as receiving excellent ratings by surrogates of acceptability, usability, and effectiveness. We will conduct a randomized trial to determine whether the multi-component intervention can improve (1) patient clinical outcomes, (2) surrogate long-term psychosocial outcomes, (3) decision and communication quality, and (4) end-of-life healthcare utilization. We hypothesize that, compared to standard ICU care, the intervention will result in increased patient-centeredness of care, decreased surrogate psychological symptom burden and decreased duration and intensity of treatment at the end of life.

## Methods

2.

### Trial design

2.1.

This is a multicenter, patient-randomized efficacy trial, funded by the National Institute on Aging (grant number R01AG06673), approved by the University of Pittsburgh Institutional Review Board (IRB; STUDY20110367), and registered on ClinicalTrials.gov (trial number NCT05019261). This trial follows the CONSORT guidelines for reporting non-pharmacological treatment interventions [19].

### Study setting

2.2.

Participants will be enrolled from 20 ICUs at 7 sites across the United States, ensuring a diverse patient population and including both community and academic hospitals. All included sites have access to palliative care, and no included sites have protocolized approaches to family communication.

### Eligibility criteria

2.3.

We will recruit 370 incapacitated, critically ill adults at high risk of death or severe disability, along with their surrogate decision-makers and their attending physician or the attending’s designee. Participants will be recruited within the first 5 days of ICU admission. Patient eligibility criteria will include age ≥ 18 years, lack of decision-making capacity as determined by clinical examination by the attending physician or designee, and clinical indication of at least 40% risk of death, or ≥ 40% chance of new, severe long-term functional impairment (needs assistance with ≥2 activities of daily living) as judged by the patient’s attending physician or designee. We will enroll one primary surrogate and up to 3 additional surrogates per patient (an average of 1.5 surrogates per patient), with the primary surrogate being decided by the patient’s advance directive or by following the hierarchy of surrogates codified in state law. Surrogates are eligible for the study both in-person and remotely. Measures to support remote participation by surrogates include:
Access to FST using a personal electronic device of their choosing, with study staff checking out a device for those who do not have a device, to be used at the hospital.If surrogates are unable to make it to the hospital, study staff will work to identify access to a device via family members or publicly available devices or computers (e.g. at a library).Family meetings may take place in-person, via conference call, or video meeting.If surrogates express difficulty completing sections of the FST, study staff will work with them either in person or remotely, depending on their ability to visit the hospital and their access to technology.

Patient exclusion criteria include lack of surrogate decision maker, family not available for study, imminent death (within 24 h), goals of care already “comfort measures only,” decision for life support withdrawal already made, current participation in competing research study, incarceration or involuntary hold, death prior to enrollment, discharge prior to enrollment, regaining of capacity prior to enrollment, physician and/or designee declining participation, more than 5 days of ICU hospitalization. Surrogate exclusion criteria include being <18 years old, not having access to a device with internet capabilities, being unable to read or understand English, and having cognitive or physical limitations impacting ability to complete study questionnaires.

### Participant screening, recruitment and consent

2.4.

A member of the research team will screen each ICU daily to identify patients meeting eligibility criteria, as we have established in prior work [20–22]. Surrogates will give proxy consent for incapacitated patients. For patients who regain capacity during the hospitalization, we will perform re-consenting.

### Intervention

2.5.

The study intervention combines 1) proactively scheduled family meetings (to increase and standardize mechanisms for communication), 2) the interactive, web-based FST for surrogates (to provide surrogate emotional support and increase decisional preparedness and understanding, as well as improve quality of communication), and 3) in-the-moment feedback and information shared with clinical teams in the form of a printed report generated by the surrogates’ responses to FST prompts and exercises that summarizes the family’s main questions and concerns, information about the patient’s values and preferences, surrogates’ prognostic expectations, and a visual display of their unmet needs (Fig. 1, Table 1).

The FST uses videos and animation, as well as narration by actor family members of ICU patients. The Cognitive Emotional Decision-Making (CEDM) Framework, the Ottawa Decision Support Framework, and input from family- and clinician stakeholders all informed the intervention’s process changes and FST (Table 1) [14,17,18]. The CEDM emphasizes the emotional and psychological influencers on decision-making, in addition to cognitive and logical ones. Families who have served as surrogates for patients hospitalized in the ICU, including patient families who faced a mix of patient outcomes (survival, different degrees of recovers, and loss of life), recorded video messages of support, communication tips, stories about their experiences and coping strategies; clinicians recorded videos of encouragement; and self-care tips were all included in the FST in order to attend to the components of this framework. The Ottawa Decision Support Framework is an evidence-based tool that supports individualized patient and family decision-making [14,17,18]. The FST includes videos explaining ICU care, routines, machines, and personnel and videos preparing surrogates for family meetings, and describing three broad potential pathways of care (comfort-focused treatment, life-extending treatment, or trial of life-extending treatment), in order to attend to key components of this framework. In addition, the FST incorporates the Ottawa Decision Support Framework with interactive exercises, prompts, and direct questions about the patient’s preferences, values and treatment leanings, which will be then shared with the clinical team.

Upon enrollment, surrogates will be oriented to the FST with a handout and with the study team. Surrogates in the intervention arm will receive unlimited access to the FST throughout hospitalization. Study staff will liaise with the enrolled surrogates and ICU team to schedule the first family meeting, within 2 days of enrollment (Table 1, Fig. 1). Family meetings may take place in person, via conference call, or via video meeting and must include the enrolled surrogates and ICU attending or their designee. Additional meeting participants will be at the discretion of the enrolled surrogates and attending. The tool was designed to be used sequentially in sections of approximately 25 min each, yet with time periods for reflection and processing interspersed. In addition, family members can review any useful sections at any time. Surrogates will be prompted to use the tool upon enrollment (section 1: about the ICU), and before the first clinician-family meeting (section 2: getting ready to talk to the healthcare team, section 3: your loved one’s values and treatment options). The study team will monitor completion and prompt family members as needed. After completing the FST, the study team will provide surrogates and ICU team members with a brief summary report containing information provided by the surrogates, such as their main questions, their preferred decision-making role, their loved one’s health-related values, their prognostic expectations and their understanding of their loved one’s treatment preference (i.e., toward life-extending care, a trial of life-extending care, or comfort-focused care). The study team will briefly review the summary with clinicians, which prompts them to address key elements of shared decision-making.

If the patient remains in the ICU on study day 5, study staff will liaise with surrogates and the ICU team to schedule the second family meeting, to take place on days 5–9 of enrollment. At least 24 h before the second scheduled family meeting, the study staff will assign the surrogates FST section 4: getting ready for your next meeting with the healthcare team. Study staff will similarly monitor surrogates’ progress and provide support for completion. On study day 5, the surrogates and ICU staff will be administered the day 5 survey (which takes 10–15 min), via REDCap, or administered by staff, assessing their understanding of their loved one’s prognosis, their opinions on the communication, the FST, and on their own decision-making. The clinician participating in the patient’s final family meeting (whether it is meeting 1 or meeting 2) will complete a brief survey (5–10 min) sharing their perspective on the patient’s clinical case and prognosis, as well as their opinions on the FST. If the patient remains in the ICU after the second family meeting, a weekly family meeting will be scheduled within 5–9 days of the previous meeting.

### Implementation support

2.6.

Prior to participant enrollment, the study team will work with ICU leadership to develop a feasible and acceptable process for coordinating family meetings with the enrolling units. Using methods informed by the pilot study, research staff will orient surrogates to the FST and be available for questions. The FST has a very simple interface and is accessible anytime and anywhere for surrogates via smartphone, tablet, or computer. If needed, surrogates had access to a tablet computer provided by research staff.

### Intervention fidelity monitoring and maintenance

2.7.

We will adhere to best practice recommendations from the NIH Behavior Change Consortium [23], to establish, monitor, and maintain intervention fidelity (Fig. 2). To establish intervention fidelity, research staff will receive training (virtually via video conference) on the detailed manual of procedures. Trainings will consist of a series of didactic sessions that included presentations, discussions, and role play. We developed a rubric that will be used in these interactive sessions, during which participant-facing coordinators will receive feedback, and will be certified only once proficiency is demonstrated. The study team will certify participant-facing coordinators by having them role play the surrogate approach, consent, and FST orientation. For each enrollment for a period of time at site initiation, coordinators will call study staff at the coordinating center to talk through their plan for intervention deployment, so that the study staff can provide feedback as needed. Coordinators will then meet biweekly throughout the study to reinforce the protocol and address issues.

The study team will monitor the surrogates’ real-time progress using customized reporting features in the FST administrative dashboard. If surrogates do not complete expected portions of the FST, the study team will offer encouragement and technical support to ensure completion before each of the goal timepoints. Similarly, study team will facilitate scheduling of family meetings per protocol, to help ensure these happen at the goal timepoints. We will quantify the amount of staff time needed for orientation of surrogates to the FST in order to gain insight into future uptake.

### Retention strategies

2.8.

We will use several strategies to maximize retention for ascertainment of trial outcomes at 3 and 6 months. These methods included short measurement instruments, telephone follow-up, and emailed and mailed surveys, with a dedicated long term follow-up team rather than in-person visits, and incremental compensation after follow-ups.

### Randomization

2.9.

Following completion of the primary surrogate’s baseline survey, study staff will randomize the enrolled patient into either the intervention group or the control group using a 1:1 randomization scheme in REDCap provided by the coordinating site. Computerized procedures will randomize participants at the patient-level, stratified by site, with 50% probability to each trial arm. Randomization procedures are designed to ensure allocation concealment prior to assignment. With 7 enrolling sites, we anticipate each site will enroll 53 patients, with 26–27 assigned to the standard care arm and 26–27 to the intervention arm. Every two additional enrollments will be randomized in the order of which arm is first assigned. To create the randomization scheme, our study statistician will use Stata to create 53 observations and then generate a random number from uniform distribution. The first 26–27 observations will be assigned to standard care and the latter 26–27 to intervention. The records will be then sorted by random number.

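### Beyond a site's 53rd patient, allocation continues in pairs, so the second assignment of each pair can be deduced, contrary to the stated allocation concealment

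*Protocol article*

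**What the plan says.** All of this stands in the protocol article, section 2.9 (Randomization), unless another section is named.

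- Allocation is 1:1 and by patient: "Computerized procedures will randomize participants at the patient-level, stratified by site, with 50% probability to each trial arm".
- Expected accrual is equal across sites: "With 7 enrolling sites, we anticipate each site will enroll 53 patients, with 26–27 assigned to the standard care arm". The trial total, in section 2.3 (Eligibility criteria), is 370.
- The site list is built as follows: "our study statistician will use Stata to create 53 observations and then generate a random number from uniform distribution". Arm totals are fixed inside it: "The first 26–27 observations will be assigned to standard care and the latter 26–27 to intervention". The records are then sorted by the random number, which makes the list one permuted block of 53.
- For enrolment past that number: "Every two additional enrollments will be randomized in the order of which arm is first assigned".
- On concealment: "Randomization procedures are designed to ensure allocation concealment prior to assignment".

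Study staff carry out the randomization in REDCap once the primary surrogate's baseline survey is complete. Under section 2.5 (Intervention), study staff also work with surrogates and the ICU team to schedule the first family meeting.

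**The concern.** Concealment requires that nobody involved in enrolment can tell the next assignment before the patient is entered. Hiding the list in REDCap achieves this only if the next entry cannot be worked out from earlier ones. In a block of two it can: once the first arm is known, the second must be the other.

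The people who could make that deduction are close to enrolment. The research team screens the ICUs daily (section 2.4), and study staff randomize and then see who receives the intervention. Entry leaves room for discretion: the 40% risk of death or severe impairment is judged by the attending or designee, the family must be available, the physician may decline, and there is a five-day window (section 2.3). Foreknowledge could therefore influence, even unintentionally, which family is approached and when. The primary outcome is a surrogate-reported scale, so a difference between arms in the kind of surrogate enrolled could bear on it directly.

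**Working it through.** **Inputs from the document.** 7 sites, 370 patients, 53 records per site with 26–27 per arm, pairs beyond 53, stratification by site.

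**The plan's own figure.** 370 / 7 = 52.86, rounded to 53; 7 × 53 = 371, one more than 370. The figure reproduces. Six sites at 53 and one at 52 give exactly 370.

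**Predictability of a pair.** The first assignment is guessed correctly with probability 0.5 and the second with probability 1 by someone who knows the first. Mean accuracy is (0.5 + 1) / 2 = 75%, and one assignment in every two is certain.

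**Predictability of the 53-record list.** Always guessing the arm with more slots left is right about 58% of the time (simulation). Assignments become certain only when one arm is exhausted. The expected number is 26/28 + 27/27 = 1.93 of 53, and only for someone who knows which arm has 27. The weakness therefore lies in the pairs.

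**How many patients are affected.** For a site enrolling n patients, the number beyond the list is max(n − 53, 0), and the number of deducible assignments is floor(max(n − 53, 0) / 2). Site totals are assumptions; each row sums to 370.

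| Assumed site totals | Beyond 53 | Deducible | Share of 370 |
|---|---|---|---|
| 53 × 6, 52 | 0 | 0 | 0% |
| Equal expected rates, chance variation (simulated mean) | about 18 | about 8 | 2% |
| 70/60/55/50/50/45/40 | 17 + 7 + 2 = 26 | 8 + 3 + 1 = 12 | 3% |
| 100/80/60/40/40/30/20 | 47 + 27 + 7 = 81 | 23 + 13 + 3 = 39 | 11% |
| 120/80/50/40/35/25/20 | 67 + 27 = 94 | 33 + 13 = 46 | 12% |

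In the equal-rates simulation (370 patients spread at random over 7 sites), the middle 90% of trials had 4 to 13 deducible assignments, and more than 99.9% had at least one.

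**Whether the 53-record list needs replacing.** Treating the list as 27 and 26 records, the hypergeometric probability that a site stopping early has an arm difference of 6 or more is set beside simple randomization:

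| Patients at the site | 53-record list | Simple randomization |
|---|---|---|
| 20 | 0.158 | 0.263 |
| 25 | 0.101 | 0.230 |
| 30 | 0.170 | 0.362 |

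The value at 25 is lower because an odd total needs a difference of at least 7. The list does control balance. Using mixed blocks of 4 and 6 for the first 53 patients instead would raise best-guess accuracy from about 58% to about 69%.

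**The case against.** The strongest reply is that the flaw is contingent. On the plan as written, no site passes 53 by enough to complete a pair, and no assignment is exposed. The document gives no site-level accrual, so every figure above zero rests on an assumed split, and the larger ones need steep splits. This stands and limits the size of the point. It does not remove the point: the pair rule applies only when a site overruns, and that is when it fails.

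Second, there are real safeguards. The statistician prepares the list, REDCap holds it, and randomization follows the baseline survey. The document does not say that site staff know the pair rule or keep count. That also stands: what is shown is that the assignment can be deduced, not that anyone has done so. But the rule is now in a published article, and REDCap cannot hide the complement of a known first assignment.

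Third, section 2.11 says outcome assessments are blinded, baseline distress and needs are measured, and section 2.13 compares baseline characteristics by arm. Blinded assessment does not protect against selection at entry. Baseline comparison may reveal selection on measured characteristics, but not on unmeasured ones.

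Fourth, the pair sentence is loosely worded. Blocks of two is its natural reading; if something else was meant, the text needs correcting anyway.

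A reader might go further and infer that the 53-record list gives no balance control, that its final entries are a material exposure, or that equal enrolment across sites is unrealistic. The document does not support these. The list roughly halves the chance of a marked imbalance at 25 or 30 patients, its end exposes about two assignments per completed site at most, and the text only anticipates 53 per site and provides for overruns.

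**Conclusion.** The point holds for the pair rule alone. Once a site has enrolled 53 patients, the second assignment of each pair is determined by the first, and staff who learn each allocation can deduce it. That contradicts the concealment statement in the same section.

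The size is 0 to 46 of 370 patients (0% to 12%) over the accrual patterns examined, with about 8 (2%) if sites recruit at equal expected rates. These figures assume the blocks-of-two reading, and they count assignments open to someone who knows the rule and keeps track. The resulting bias in the primary outcome has not been estimated and cannot be from the document. It would be wrong to conclude that concealment fails throughout the trial: the first 53 patients at each site are little affected, and so is the first patient of each pair.

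**What to change.** Replace the sentence on additional enrolments. The statistician should extend each site's REDCap list past any plausible enrolment, using permuted blocks larger than two, of randomly varying size, with the sizes withheld from site staff and from published text. Leave the 53-record list as it is.

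If enrolment has begun, apply the extension to unallocated slots only, and report which patients, at which sites, were assigned in pairs.

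The cost is one list upload, one changed sentence in the protocol, and slightly looser arm balance at the end of a site's enrolment than pairs would give. Blocks of varying size can still be guessed better than chance (about 68% for mixed blocks of 4, 6 and 8, against 75% for known pairs), but someone who does not know the sizes can no longer deduce every second assignment with certainty.
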